### Objectives and hypotheses

The objective of the proposed trial is to address depression symptoms in patients with obesity and provide a low-threshold e-mental health intervention. We aim to assess the efficacy of the e-mental health intervention LightMood in patients with obesity and depression symptoms.

The primary hypothesis is that we expect the LightMood intervention to be superior to TAU in terms of reducing depression symptoms (T1) in patients with obesity.

Secondary hypotheses are that we expect the LightMood intervention to be superior to TAU in terms of improving self-efficacy, quality of life, mindfulness, reducing eating disorder symptoms, and reducing body mass index (BMI). Furthermore, we expect a positive development of depression symptoms throughout the different time points (T1, T2, and T3) in patients with obesity. All in all, it is expected to reach improvement by T1 and sustained gains at T2 and T3.

Other study goals are to evaluate client satisfaction, usability, and adherence of and to the LightMood intervention. Furthermore, we will assess usage behavior and explore relations between the observed usage behavior and other study outcomes.

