#### Sample size calculation

The calculation of the sample size was performed using the R-package “Superpower” [38]. Our primary hypothesis is that the intervention will be superior in terms of reducing depression symptoms compared to TAU (control group) at T1. To assess the efficacy of the intervention, we will conduct an ANCOVA analysis with the primary outcome variable at T1 as the dependent variable, the group variable (intervention vs. control group) as a between-subject factor, and the individual baseline levels at T0 as a covariate. Subsequently, a mixed ANOVA analysis with the respective measurements (T0–T3) as a within-subject factor and the group variable as a between-subject factor will be used to explore the intervention’s effect at follow-up.

For the sample size calculation, we selected a preferred test power of 1 − *ß* = 0.80. We anticipate a moderate effect size of *d* = 0.5 for the baseline-adjusted comparison between the intervention and control group at T1. Based on previous studies, we expect the correlation between repeated measures to be *r* = 0.5 [39].

According to the power analyses, a total effective sample size of *n* = 98 (49 participants per group) will provide a statistical power of 80.34 for the ANCOVA analysis mentioned above. With the same number of participants, we achieve a power of 95.8 for the mixed ANOVA analysis mentioned earlier, assuming a conservative assumption that the sole difference between the intervention and control group occurs at T1.

Considering a dropout rate of 30% from T0 to T3, based on existing literature on eHealth trials [40], we estimate that 128 participants (64 per group) will be required. This dropout rate includes loss to follow-up.

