#### Statistical methods

The primary objective of this trial is to evaluate the efficacy of the intervention in terms of reducing depression symptoms after the intervention, compared to the control group. To achieve this, we will employ an analysis of covariance (ANCOVA) with the outcome measured at T1, using the between-subject factor of the group (intervention vs. control) and the participants’ baseline values (T0) as a covariate. The primary analysis will be conducted on the intention-to-treat population, with missing data imputed in cases of dropout. Imputation will be performed using the SPSS multiple imputation module, employing “monotone missing pattern” and incorporating complete data for sex, age, and baseline measurements of primary and secondary outcomes. The imputation process will be executed with 3000 imputations, using the analysis date as the seed. Interim analyses are not planned.

Subsequent mixed ANOVAs will be conducted with a between-subject factor representing group membership (intervention vs. control) and a within-subject factor corresponding to the respective measurement points (T0–T3). These analyses will assess whether the effects of the intervention are sustained during the follow-up period. Similar approaches will be applied for the analysis of additional clinical endpoints. In the event of substantial deviations from normality or homoscedasticity assumptions, non-parametric tests, robust procedures such as robust regression analyses, generalized estimating equations, or robust mixed linear models will be employed instead. Corrections, such as Huynh-Feldt or Greenhouse-Geisser, will be implemented if the assumption of sphericity is violated in the mixed ANOVA.

Descriptive analyses will be conducted to assess treatment satisfaction, usability, and usage behavior. For comparisons of demographic and baseline parameters between the two groups, *t*-tests (or Mann-Whitney *U*-tests in the case of non-normality) and *χ*

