^2^ tests (or Fisher’s exact tests for variables with small cell sizes) will be utilized. Further mixed ANOVAs will be used to assess the impact of the intervention on the secondary outcome measures, such as eating behaviors (see Table 1). Also here, we will resort to more robust models in case of a violation of assumptions. Also, in case of a significant effect of our intervention on the primary outcome, we will assess whether this result is mediated by increases or decreases in scores concerning eating behavior. Here, we will use mediation analyses on mixed linear models or robust alternatives (such as mixed linear models with bootstrapping). We will not perform subgroup analyses. Additionally, analyses of variance and *χ*
^2^ tests will be employed to examine potential differences in sociodemographic and clinical data among various subgroups, such as dropouts, participants who completed the intervention, and those who benefitted from the intervention.

Exploratory analyses, including regression analyses, will be conducted to investigate the relationship between usage behavior and clinical outcomes, considering all assessments including in-treatment assessments. Secondary endpoints will include the examination of time to dropout using the Kaplan-Meier estimate and Cox proportional hazards regression. Here, a standard proportional hazards model—using the *coxph* function from the *survival* package in R—will be applied. Differences in time to dropout between the treatment and the control group will be assessed. Also, the baseline values of the relevant psychometric measures of depression and mental distress (CESD-R, PHQ-4, DT), self-efficacy (GSES), quality of life (WHOQOL), and eating behavior (EDI-2, EDE-Q8), as well as sociodemographic and medical characteristics (gender, SES, BMI), will be entered into the regression model to explore potential determinants of dropout. In case of large deviations from constant hazards (which will be tested using the *cox.zph* function from the abovementioned package), we will explore underlying reasons and might, for instance, further assess non-linear effects or models with stratification according to certain covariates.

To ensure safety assessment, separate tabulations and line listings of adverse events and severe adverse events will be generated for comprehensive analysis.

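### The T0–T3 group × time test is equally likely to be significant whether the effect persists or vanishes, so sustained gains need named T2 and T3 comparisons

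*Protocol article*

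**What the plan says.** Under Objectives and hypotheses, the secondary hypotheses close with the statement that "it is expected to reach improvement by T1 and sustained gains at T2 and T3".

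Under Statistical methods, the primary outcome is analysed by ANCOVA at T1 with the T0 value as covariate. Mixed ANOVAs then follow, with group as the between-subject factor and the four assessments T0 to T3 as levels of the within-subject factor. Their purpose is given as: "These analyses will assess whether the effects of the intervention are sustained during the follow-up period". No contrast, time-specific comparison or change from T1 to T3 is named. The same type of model serves the other endpoints: "Further mixed ANOVAs will be used to assess the impact of the intervention on the secondary outcome measures".

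The Sample size calculation section gives the mixed ANOVA the task of exploring the effect at follow-up. It reports a power of 95.8% for it, "assuming a conservative assumption that the sole difference between the intervention and control group occurs at T1".

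Multiple imputation is described in the sentences on the primary analysis. Whether it also feeds the mixed ANOVAs is not stated.

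**The concern.** In a group × time ANOVA with baseline as one of the times, the test that carries the treatment effect is the interaction. With four times it has three degrees of freedom. It asks whether the group difference is constant over T0–T3, and it rejects for any departure from constancy. A difference that appears at T1 and is gone at T2 and T3 is such a departure, and it is the very pattern on which the analysis was powered.

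So the stated power is the chance of a significant result when nothing is sustained. If a significant interaction were offered as support for lasting benefit, the hypothesis about T2 and T3 would not have been tested. For the secondary superiority hypotheses the same test has no direction, and it spreads its power over three degrees of freedom where a baseline-adjusted T1 comparison needs one.

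**Working it through.** **Inputs** (Sample size calculation unless noted)
- n = 49 per group, 98 in total.
- Effect: "We anticipate a moderate effect size of *d* = 0.5 for the baseline-adjusted comparison" at T1.
- Correlation: "we expect the correlation between repeated measures to be *r* = 0.5". A single value for all pairs means compound symmetry, so sphericity holds.
- SD set to 1, so that differences are in units of d.
- Alpha: not stated; two-sided 0.05 assumed.

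**Step 1: the plan's own figures.**

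ANCOVA at T1: noncentrality λ = (n/2)·d²/(1 − r²) = 24.5 × 0.25/0.75 = 8.17, with F(1, 95). This gives 80.8%. Averaging over chance baseline imbalance gives 80.34%, which matches the protocol's 80.34 and supports the assumed alpha.

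Mixed ANOVA, interaction: λ = (n/2)·Σ(δt − mean δ)²/[SD²(1 − r)], with F(3, 3(2n − 2)) = F(3, 288), where δt is the group difference at time t. For a T1-only effect, λ = 9.19 and power is 71.5%, so the stated 95.8% is not reproduced. With the stated d and r, 98 per group comes close (λ = 18.375, 96.2%). That discrepancy is a separate matter, and nothing below depends on it.

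**Step 2: vanishing against persisting effect.**
- Gone after T1, δ = (0, 0.5, 0, 0): mean 0.125; squared deviations 3 × 0.125² + 0.375² = 0.1875.
- Fully kept, δ = (0, 0.5, 0.5, 0.5): mean 0.375; squared deviations 0.375² + 3 × 0.125² = 0.1875.
- In both cases λ = 24.5 × 0.1875/0.5 = 9.1875 and power = 71.5%.

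Both sums equal 0.75d², so under a common correlation the equality is exact for any n, d and r: 55.3% each at r = 0.3, 91.9% each at r = 0.7.

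**Step 3: other patterns and the main effect.** For the group main effect, λ = (n/2)·(mean δ)²/[(1 + 3r)/4], with F(1, 96) and (1 + 3r)/4 = 0.625.

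| Group difference at T0, T1, T2, T3 | Interaction λ | Interaction power | Main-effect λ | Main-effect power |
|---|---|---|---|---|
| 0, 0.5, 0, 0 (gone after T1) | 9.19 | 71.5% | 0.61 | 12.1% |
| 0, 0.5, 0.25, 0.25 (half kept) | 6.13 | 52.1% | 2.45 | 34.1% |
| 0, 0.5, 0.5, 0 (kept at T2, lost at T3) | 12.25 | 84.3% | 2.45 | 34.1% |
| 0, 0.5, 0.5, 0.5 (fully kept) | 9.19 | 71.5% | 5.51 | 64.2% |

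Interaction power does not rise with persistence. An effect lost by T3 is more likely to be significant than one fully kept.

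**Step 4: unequal correlations (simulation, uncorrected F; vanishing against persisting).**
- AR(1) with 0.5: 60% against 56%.
- AR(1) with 0.7: 82% against 76%.
- 0.7 between post-baseline times and 0.5 with baseline: 84% against 75%.

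The equality is then only approximate. In each case the vanishing effect was the more likely to be significant, and the Greenhouse-Geisser correction did not change the direction.

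**Step 5: a direct comparison.** Baseline-adjusted ANCOVA at T3 with 49 per group uses the same λ = 8.17. Power is about 80% if d = 0.5 persists, and the rejection rate is 5% if the effect has vanished.

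**Step 6: secondary outcomes.** For a T1-only or fully sustained d = 0.5, the T1 ANCOVA has 80.3% power and the omnibus interaction 71.5%.

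**Step 7: if there is no imputation.** A standard repeated-measures ANOVA uses only participants with all four assessments. At the assumed 30% dropout that is at most 128 × 0.70 = 89.6, about 90 participants.

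**The case against.** The protocol does not say that a significant interaction will be read as persistence. A 2 × 4 ANOVA also yields a group main effect, estimated means by group and time, and follow-up contrasts. Those contrasts may be set out in a statistical analysis plan that is not shown. This stands as a limit on the claim: means or contrasts from the same model could show persistence. It does not remove the point, because the article assigns the question to the mixed ANOVA itself and justifies that analysis by power under an effect confined to T1.

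A reader might infer that the mixed ANOVA carries no information on persistence. That goes too far. The main effect separates the two scenarios, 12.1% against 64.2%. It is still a poor test of follow-up, since it includes T0, where randomisation makes the expected difference zero, and it mixes T1 with T2 and T3.

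A reader might also infer that follow-up and secondary analyses will rest on completers. The document does not support this. Imputation is described only under the primary analysis, but listwise deletion is nowhere stated. The imputation model includes secondary-outcome baselines, and similar approaches are promised for other endpoints. The figure of about 90 is therefore conditional.

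Finally, treating baseline as a level of time is valid in a randomised trial, because the interaction tests differential change. The charge for secondary outcomes is lower efficiency, not error, and it depends on the pattern: an effect kept at T2 and lost at T3 gives the interaction 84.3%.

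**Conclusion.** The point holds for the omnibus group × time interaction. Under the protocol's assumptions its chance of significance is 71.5% whether the effect disappears after T1 or persists in full, so taken alone it cannot support the sustained-gains hypothesis. The equality is exact under one common correlation. Under the unequal correlations simulated it was approximate, and it favoured the vanishing effect. The 71.5% figure rests on 49 per group, d = 0.5, r = 0.5 and an assumed two-sided alpha of 0.05.

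It would be wrong to conclude that the trial's main result is at risk. The confirmatory test is the baseline-adjusted ANCOVA at T1, which is untouched, and sustained gains are a secondary hypothesis. This is a should-fix point for the follow-up and secondary analyses.

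**What to change.** - **Sustained gains.** Name the baseline-adjusted group difference at T2 and at T3, each with a 95% confidence interval, as the test of this hypothesis. Either of two routes would serve: a longitudinal mixed model on T1–T3 with baseline as covariate and group, time and group × time, using all available data; or ANCOVA at each time on multiply imputed data, with the imputation extended to T2 and T3.
- **Interpretation.** State that a significant omnibus interaction will not be read as evidence of persistence.
- **Secondary outcomes.** Test superiority by the same baseline-adjusted T1 contrast as the primary outcome.
- **Missing data.** State how missing assessments are handled in the follow-up and secondary analyses.

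The cost is a few sentences, agreed before anyone sees outcome data by group. No further data or participants are needed for this change. If the mixed model is fitted with an unstructured covariance, the planned sphericity corrections are no longer needed.

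### The group-by-time interaction over T0–T3 cannot separate a lost from a kept depression effect, yet the mixed ANOVA is the only analysis named for whether the effect is sustained

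*Protocol article*

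**What the plan says.** The *Objectives and hypotheses* section of the protocol article places the course of depression symptoms over T1, T2 and T3 among the secondary hypotheses and adds that "it is expected to reach improvement by T1 and sustained gains at T2 and T3".

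The *Statistical methods* section makes the T1 ANCOVA with T0 as covariate the primary analysis. It then plans mixed ANOVAs with group as between-subject factor and the four measurement points T0 to T3 as within-subject factor, and gives their purpose: "These analyses will assess whether the effects of the intervention are sustained during the follow-up period". It does not say which term of the model answers that question, names no group comparison at T2 or T3, and gives no criterion for calling an effect sustained. Similar approaches are announced for the other clinical endpoints.

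The *Sample size calculation* section gives the same mixed ANOVA the task of exploring the effect at follow-up. It credits that analysis with 95.8% power at 49 per group. The scenario behind this figure is given in these words: "assuming a conservative assumption that the sole difference between the intervention and control group occurs at T1".

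**The concern.** Whether an effect is sustained is a question about the difference between groups at T2 and T3. The interaction of a four-point mixed ANOVA answers another question: whether the two group profiles are parallel across all four points. A difference that appears at T1 and is gone by T2 breaks parallelism just as a difference that appears at T1 and stays does.

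The power statement shows the mismatch in the protocol's own terms. An analysis meant to show durability is credited with high power in a scenario where no group difference exists at either follow-up visit. If the test is expected to be significant there, its significance cannot be evidence that gains last.

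At stake is the durability conclusion, which is a stated hypothesis and the main use of the T2 and T3 assessments.

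**Working it through.** **Inputs.** All but alpha come from the *Sample size calculation* section.
- Effect: "We anticipate a moderate effect size of *d* = 0.5 for the baseline-adjusted comparison between the intervention and control group at T1".
- Correlation: "we expect the correlation between repeated measures to be *r* = 0.5", read as one common value for every pair of visits.
- Effective sample: n = 49 per group, 98 in total.
- Alpha is not stated; 0.05 two-sided is assumed. The outcome SD is set to 1, and differences are written as benefit for LightMood.

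**Step 1: the plan's own figures.**
- ANCOVA at T1: noncentrality λ = (n/2)·d²/(1 − r²) = 24.5 × 0.25/0.75 = 8.17, with 1 and 95 degrees of freedom. Power is 80.8%, against 80.34% stated. This reproduces, which supports the reading of the inputs.
- Mixed ANOVA, T1-only difference: step 2 gives 71.5% for the interaction at 49 per group, against 95.8% stated. This does not reproduce. With 98 per group the interaction would reach 96.2%. That discrepancy is a separate matter, and nothing below depends on it.

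**Step 2: interaction.** λ = (n/2)·SS/(1 − r), where SS is the sum of squared deviations of the group differences (T0, T1, T2, T3) from their mean; degrees of freedom are 3 and 3(2n − 2) = 288.
- Effect lost after T1, (0, 0.5, 0, 0): mean 0.125; SS = 0.375² + 3 × 0.125² = 0.1406 + 0.0469 = 0.1875.
- Effect fully kept, (0, 0.5, 0.5, 0.5): mean 0.375; SS = 0.375² + 3 × 0.125² = 0.1875.
- In both cases λ = 24.5 × 0.1875/0.5 = 9.19 and power is 71.5%.

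The equality does not depend on d, n or alpha: one differing visit out of four and three equally differing visits out of four have the same spread around their mean. At 64 per group both powers are 83.6%.

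**Step 3: group main effect.** λ = (n/2)·4·(mean difference)²/(1 + 3r), with 1 and 96 degrees of freedom.
- Lost: 24.5 × 4 × 0.125²/2.5 = 0.61; power 12.1%.
- Kept: 24.5 × 4 × 0.375²/2.5 = 5.51; power 64.2%.

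This term does respond to a kept effect. But it averages over T0, which precedes randomization, and over T1, which the primary analysis already tests. It also cannot be the term behind the stated power: under a T1-only difference it has 12% at 49 per group and about 20% even at 98 per group.

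**Step 4: unequal correlations.** If correlation decays with the spacing of visits (months 0, 4, 5 and 7; 0.5 at four months, an assumption) and the Greenhouse-Geisser correction is applied, simulated power of the interaction is about 77% when the effect is lost and 65% when it is kept. The equality is then gone, but in the unhelpful direction.

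**Step 5: a direct contrast on the same inputs.** A baseline-adjusted group difference at T3 has λ = 8.17 and 80.8% power if the effect is kept. If it is lost, the contrast rejects in 5% of trials, 2.5% in favour of LightMood.

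**The case against.** The strongest reply is that the protocol states no decision rule. It names a model and a purpose, but neither the interaction nor an omnibus p-value as the criterion. A mixed ANOVA also yields a group main effect, cell means and contrasts, and the choice among them is detail that an article may leave to the statistical analysis plan, which is said to be available on request and is not shown here. The authors would also see their own T2 and T3 means, and a complete relapse would be visible in them. Finally, the T1-only pattern is a power scenario described as conservative, not a rule of interpretation, and the analysis is exploratory and secondary.

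Much of this stands. A reader might infer that the mixed ANOVA as a whole is blind to the difference between a lost and a kept effect. It is not, because the group main effect is 12% against 64%. The exact equality holds for the interaction only, and only under a common correlation. A reader might also infer that a relapse will be reported as a sustained effect. The document does not say so; it leaves that possible.

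What does not stand is that this is merely missing detail. The published text assigns the durability question to this analysis and powers it on a pattern with no follow-up effect. Neither group term of the model tests maintenance. Contrasts chosen once the means are known would not be a prespecified answer to a stated hypothesis.

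**Conclusion.** The point holds for the group-by-time interaction. Under the protocol's d = 0.5, common r = 0.5 and 49 per group, with alpha 0.05 two-sided assumed, the interaction is significant with probability 71.5% whether the effect is wholly lost or wholly kept after T1. A significant result therefore carries no information on which of the two happened, and could be read as durability after a complete relapse. The group main effect distinguishes the two cases but is not a test of maintenance.

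The consequence is limited to a secondary hypothesis, and to other clinical endpoints where the same approach is used to claim maintenance. It would be wrong to extend it to the main result: the primary T1 ANCOVA does not use this model and is unaffected. The change should be made, but the point does not threaten the trial's primary conclusion.

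**What to change.** In *Statistical methods*, replace the sentence on sustained effects with three statements:
- A sustained effect on the CESD-R is judged by the baseline-adjusted LightMood minus TAU differences, with 95% confidence intervals, at T2 and at T3. These come from separate ANCOVAs or from one mixed model with T0 as covariate.
- The effect is called sustained only where the interval at both T2 and T3 excludes zero in favour of LightMood.
- The omnibus interaction is not used as evidence of durability.

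The mixed ANOVA may stay as a description of the course over time.

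This is a change of wording and needs no further data, visits or participants. The cost is that a durability claim becomes somewhat harder to reach. With r = 0.5 throughout, the baseline-adjusted T2 and T3 outcomes correlate at (0.5 − 0.25)/0.75 = 1/3. By the normal approximation, each contrast is significant when a standard normal deviate lies below √8.17 − 1.96 = 0.90, and both are significant with probability about 0.69 if the effect is fully kept (0.67 by simulation), against about 0.81 for T3 alone.

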### Study design

The study is an online-based study, which is coordinated in the clinic for psychosomatic medicine and psychotherapy, LVR-University Hospital Essen, University of Duisburg-Essen in Essen, Germany. The study comprises a prospective, randomized controlled trial with two parallel arms. The proposed trial incorporates four distinct measurement time points: the baseline assessment (T0) before randomization, a post-treatment assessment (T1), and a 1-month and 3-month follow-up assessment (T2 and T3). Additionally, continuous assessments are planned during the experimental and control intervention (in-treatment assessment); Table 1 gives an overview of the assessment schedule.

**Table 1 Tab1:** Overview of the assessment schedule

Measures	Baseline	In-treatment assessment	End of treatment	Follow-up assessments	Drop-out assessment

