#### Outcomes

The primary outcome is the reduction in depression symptoms at the end of treatment (T1; see Table 1). To measure *depression symptoms*, we will use the German Version of the Center of Epidemiologic Studies Depression Scale—Revised [24]. The CESD-R is a valid measurement instrument, used to record the diagnosis and severity of depression disorders according to DSM-5 in clinical studies [25, 26]. The CESD-R consists of 20 items covering nine different symptom areas [24].

Secondary endpoints for this study include (1) self-efficacy, (2) quality of life, (3) mindfulness, (4) eating disorder symptoms, (5) BMI, (6) treatment satisfaction, (7) usability, (8) usage behavior, (9) predictors of usage behavior, and (10) course/development of depression symptoms. All scales used are presented in German.
*Self-efficacy*: for the assessment of self-efficacy, we will use the German version of the General Self-Efficacy Scale [27]. The GSES is a self-report measure of self-efficacy and optimistic self-beliefs related to coping with a variety of difficult demands in life as well as coping with all kinds of stressful life events. Responses are rated on a 4-point Likert scale for all 10 items.
*Quality of life*: The World Health Organization Quality Of Life Questionnaire [28] is used to assess quality of life. The WHOQOL assesses the individual’s perception of their own position in life in the context of the culture and value systems in which the person lives and in relation to their goals, expectations, norms, and concerns. The WHOQOL measures life satisfaction and self-esteem using 26 items. Items are rated on a 5-point Likert scale from 1 (low satisfaction) to 5 (high satisfaction).
*Mindfulness:* to assess mindfulness, we will use the validated German version of the Freiburg Mindfulness Inventory [29]. It consists of 14 items, and all responses are given on a 4-point Likert scale.

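### The planned mediation of the T1 depression effect by eating-behaviour change cannot establish direction, because the first eating score after randomisation is taken at the same assessment as the outcome

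*Protocol article*

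**What the plan says.** The protocol article fixes the primary outcome in time: "The primary outcome is the reduction in depression symptoms at the end of treatment (T1; see Table 1"). Under Statistical methods the mediation analysis is conditional on a significant effect on that outcome: "we will assess whether this result is mediated by increases or decreases in scores concerning eating behavior". The mediator is change in eating-behaviour scores. The method is given as "we will use mediation analyses on mixed linear models or robust alternatives (such as mixed linear models with bootstrapping"). No wave is named for the mediator, and no lag is stated.

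Table 1 (Study design) gives the schedule. EDI-2 and EDE-Q8 are marked at baseline, end of treatment and follow-up, and their in-treatment cells are empty. The CESD-R is marked at the same three points and at drop-out. Only usage behaviour, the PHQ-4 and the distress thermometer are collected during treatment, and none of these measures eating. After T1 there is "a 1-month and 3-month follow-up assessment (T2 and T3").

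**The concern.** Mediation is a claim about order: treatment changes eating, and the change in eating then changes depression. Testing it for the T1 effect needs an eating score taken after randomisation and before the T1 CESD-R. The schedule has none.

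The reverse order is plausible on the article's own terms. The Background describes the relation between depression and obesity as reciprocal, and the Emotions module in Table 2 teaches participants how emotions influence eating. If treatment lifts mood and better mood reduces binge eating, T1 eating scores will differ between groups and will correlate with T1 CESD-R within groups. Those are the two patterns that a mediation analysis reads as an indirect effect. At stake is how a positive trial would describe its mechanism. The primary comparison is not in question.

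**Working it through.** **1. The plan's own figure.** The mediation analysis has no stated figure. The primary ANCOVA does, and its inputs are used below. They are: "We anticipate a moderate effect size of *d* = 0.5 for the baseline-adjusted comparison between the intervention and control group at T1"; "we expect the correlation between repeated measures to be *r* = 0.5"; 49 per group; stated power 80.34%. The significance level is not given, so two-sided 0.05 is assumed.
- Residual SD = √(1 − 0.5²) = 0.866, so the standardised effect is 0.5/0.866 = 0.577.
- Noncentrality = 0.577 × √(49/2) = 2.86 on 95 degrees of freedom.
- Power = 80.8%, close to the stated 80.34%.

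**2. The schedule set against the question.**

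| Score | T0 | In treatment | T1 | T2, T3 |
|---|---|---|---|---|
| EDI-2, EDE-Q8 (mediator) | yes | no | yes | yes |
| CESD-R (outcome) | yes | no | yes | yes |

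No eating score lies strictly between T0 and the T1 CESD-R. T2 and T3 eating scores come after the T1 outcome and cannot mediate it. The only post-randomisation eating score available for the T1 effect is the T1 score.

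**3. What a same-wave analysis returns when true mediation is zero.** Let treatment shift T1 depression by τ = −0.5 SD. Let eating change follow depression change with coefficient k, with equal residual SDs (√0.75) for both. The protocol gives no value for k.
- Group-to-mediator path: kτ.
- Mediator-to-outcome slope, given group and both baselines: k/(1 + k²).
- Apparent indirect effect: τk²/(1 + k²), a share of k²/(1 + k²) of the total effect.

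The simulation used 98 participants and kept trials with a significant primary effect. It called mediation present when both paths were significant at 5%.

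| k | Share by formula | Simulated share | Mediation declared |
|---|---|---|---|
| 0 | 0 | 0% | 0.3% |
| 0.3 | 0.09/1.09 = 8.3% | 8% | 12% |
| 0.5 | 0.25/1.25 = 20.0% | 20% | 27% |
| 0.7 | 0.49/1.49 = 32.9% | 33% | 44% |

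A separate set of runs for k = 0.3 to 0.7 gave shares of about 7% to 32% and mediation declared in about 13% to 40%. The overall range of shares is therefore roughly 7% to 33%. With 2,000 participants and k = 0.5 the share stays at 20% and mediation is declared in every trial. This is bias, and a larger sample does not remove it.

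**4. Whether the later waves repair it.** Take the opposite truth, in which eating change carries the whole T1 effect. Assumptions: 98 participants, a 1.0 SD treatment shift in eating, an eating-to-depression slope of 0.5, T2 depression depending only on T1 CESD-R, and no measurement error. A lagged model (T0–T1 eating change to T2 CESD-R, adjusted for T1 CESD-R) declares mediation in about 5% of trials with a significant primary effect. The same-wave model declares it in more than 99%. Adjusting for T1 CESD-R removes the effect that was to be explained.

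**The case against.** The article never states a regression of T1 outcome on T1 mediator. It names no wave, and mixed linear models suggest data from several waves. An analysis plan that is not shown could specify a lag. This limits what can be said about the model form, but it does not remove the point. The analysis is tied to the primary result, which is the T1 effect, and no analysis plan can supply an eating score that was never scheduled. Pooling T0–T3 without a lag still relates scores from the same wave.

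The EDE-Q8 partly asks about the past 28 days, so its T1 score looks back into treatment. Those days fall late in a four-month intervention, when mood may already have changed, so order is still not established.

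Mediation appears neither among the hypotheses nor among the listed endpoints, and the article says only that it will be assessed. That stands: nothing commits the team to reporting a proven mechanism, and the point is minor.

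Two stronger readings are tempting. One is that the analysis cannot show mediation at all. This goes too far, because concurrent data can be consistent with mediation; they cannot separate it from the alternatives. The other is that T2 and T3 already hold the data for a proper test, so a lagged model should replace the T1 analysis. Step 4 of the working shows why that fails: the lagged model asks whether eating change predicts further depression change after treatment, and it can miss complete mediation of the T1 effect. It would also leave all measures as self-reports.

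**Conclusion.** The point holds in limited form. From the schedule alone, with no assumption, the first eating score after randomisation shares its assessment with the T1 CESD-R. An indirect effect on the T1 result therefore cannot establish direction. The size is illustrative: roughly 7% to 33% of the effect would be attributed to eating when the true mediated share is zero. This assumes purely reverse causation, k between 0.3 and 0.7, and a same-wave model. None of the protocol's figures changes, and the primary conclusion is unaffected. This is a worthwhile clarification of a conditional secondary analysis.

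**What to change.** Add one sentence after the mediation text in Statistical methods: any mediation result for the T1 effect is exploratory and will be reported as a concurrent association that does not establish direction.

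Optionally, add a supplementary lagged analysis. It would relate T0–T1 change in EDI-2 and EDE-Q8 to CESD-R at T2 and T3, adjusted for the baseline mediator, baseline CESD-R and T1 CESD-R. It should be labelled as an analysis of later depression change. It should not be presented as a test of what mediates the T1 effect, and it should not replace the T1 analysis.

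The cost is wording and a weaker statement about mechanism. The supplement needs no new measurements, but it would face more missing data at T2 and T3.
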